#### Primary outcomes

The primary outcome for the trial is the difference in 24-h ambulatory SBP after 8 weeks of exercise training compared to control. SBP is a stronger predictor of end-stage renal disease than DBP or other measures of arterial stiffness in people with CKD [1–3, 32]. Twenty-four-hour ABPM is the gold-standard method for BP measurement and more accurately predicts renal and CV risk in people with CKD than clinic BP [33]. Participants will be advised to perform their regular daily routine (but not to exercise) during the 24-h ABPM period or 24 h before the study visit (for clinic BP measurements). ABPM will be measured using a validated device (OnTrak Ambulatory Blood Pressure Monitor 90,227–1; Spacelabs Healthcare, Mississauga, ON, Canada) [34] worn on the non-dominant arm for a 24-h period. Readings will be obtained at 20-min intervals from 6 a.m. to 10 p.m. and at 30-min intervals from 10 p.m. to 6 a.m. according to a recommended protocol [35].

#### Secondary outcomes

##### Additional blood pressure and vascular outcomes

The difference in overall, daytime, nighttime ABPM, and clinic BPs at 8 and 24 weeks will be reported. Clinic BPs will be measured using the mean of three readings (after discarding the first reading), each 1 min apart. Arterial stiffness will be estimated using the pulse-wave velocity (PWV) between the (1) carotid and femoral and the (2) carotid and radial arteries with the Complior device. Recommendations for the conditions and measurement of PWV will be followed [36]. Mean PWV will be calculated as the average of at least 10 consecutive beats in order to cover a full respiratory cycle.

##### Changes in anti-hypertensive drugs

The Defined Daily Dose (DDD) of anti-hypertensive drugs will be used to calculate any changes to BP medications during the study [37]. Medication lists will be collected from the participant and verified with the pharmacy record (available through an electronic provincial data repository) at each study visit. At study visits, a brief questionnaire designed to capture both intentional and non-intentional medication adherence will be administered [38].

##### Markers of cardiovascular risk

Body Mass Index (BMI), C-reactive protein, hemoglobin A_1_C (HgA_1_C) (only participants with diabetes) and lipid profile. Urine studies include spot urinary sodium, protein, and creatinine. All samples will be collected according to routine laboratory protocol on a non-exercise day after an overnight fast. To measure fat-free mass, whole-body bioimpedance measurements will be performed using the Body Composition Monitor (BCM; Fresenius Medical Care, Germany).

##### Cardiorespiratory fitness

Peak VO_2_ (volume of oxygen consumption) using a calibrated TrueOne 2400 metabolic cart (ParvoMedics TrueOne, Murray, UT, USA) from the CPET will be used to evaluate exercise-training adaptations and to determine the dose of exercise that was performed. The preferred modality for the CPET will be a stationary bicycle. After 5 min of rest, participants will start cycling at 10 W with an increasing stepped workload of 10–20 W every 2 min. The CPET will be symptom-limited, with the aim of achieving a respiratory exchange ratio > 1.10 and a Borg Rating of Perceived Exertion greater than 8 on a 0–10 scale. VO_2_ will be defined as the highest oxygen uptake value recorded during the test. VO_2_ peak will be derived from breath-by-breath indirect calorimetry and recorded as the peak 20-s average VO_2_ during the final minute of exercise. Using the post-CPET heart rate recovery at 1 and 5 min, we will also explore the parasympathetic response to exercise. Other measures of functional capacity in the exercise group include the 6-min Walk Test [39], performed three times during phase 1 and once at the end of phase 2.

##### Physical activity and adherence

Accelerometry (Actigraph® GT3X+ Actigraph, LLC, Pensacola, FL, USA) will be used to measure the overall difference in physical activity levels between groups and adherence in the intervention group. Participants will be instructed to wear the Actigraph device around the waist for at least 10 waking hours for seven consecutive days. Best practice and research recommendations on the management and analysis of physical activity data will be followed [40]. In phase 1, adherence will be measured as the proportion of people who attended all eight in-center sessions within 12 weeks. For the home components of phase 1 and phase 2, adherence will be assessed as the proportion of exercise sessions completed at the prescribed frequency, time, and intensity over 7 days/number of exercise session prescribed (as measured by accelerometry). Data from participant logbooks will be used to explain any discrepancies in the accelerometry data and to provide a similar calculation of adherence overall. To determine adherence, a threshold of 70% of sessions attended and 70% of sessions performed as prescribed will be applied.

Following 7-day accelerometry, participants will complete the International Physical Activity Questionnaire Short Form (IPAQ-SF) [41]. The IPAQ-SF contains seven items that assess physical activity over the previous 7 days. Four intensity levels of activity, including sedentary behavior, are evaluated. It is the most widely used scale to monitor physical activity, thereby facilitating comparisons between populations [42].

##### Quality of life

The Kidney Disease and Quality of Life Instrument (KDQOL-36) tool includes the 12-item Short Form Health Survey (SF-12) as generic core plus symptoms/problems of kidney disease scales [43]. The KDQOL-36 is a valid and reliable disease-specific questionnaire and has been extensively used in people with non-dialysis CKD [44]. Preference-based utilities will be measured by the EQ-5D (EuroQol Health Questionnaire) [45].

##### Adverse events

Adverse events (AEs) are defined as any unfavorable or unintended event affecting study participants. Major AEs include death, hospitalization (unplanned), emergency department visits, CV events (stroke, myocardial infarction); doubling of serum creatinine from baseline; permanent disability; syncope, arrhythmia. Minor AEs include symptomatic hypoglycemia, hyper- or hypotension requiring medical attention, musculoskeletal injury, pre-syncope during or within 1 h after exercise. Due to the low risk of the intervention we will not use a data safety and monitoring board. All serious adverse events will be forwarded to a physician who is not involved in the trial. The physician will adjudicate whether the event was due to the exercise treatment, facilitate the necessary medical follow-up, and determine whether participation should be modified.

##### Feasibility criteria

To inform the design of a future trial on the effect of exercise on the progression of CKD, we will evaluate enrollment, adherence, drop out and missing data using the following criteria: 30% of people screened are randomized [46] drop out less than 20%, missing outcome data less than 10%, and adherence to exercise sessions greater than 70% (as described above).

##### Exploratory

eGFR using the Chronic Kidney Disease Epidemiology Collaboration (CKD-EPI) equation for creatinine and cystatin C [47, 48].

### Sample size

The sample size calculations for this trial are based on data from exercise and lifestyle modification trials in hypertensive populations [49–51]. As a 5-mmHg reduction in BP in high-risk patients reduces CV events by 15% [52], this study is powered to detect a clinically important difference in mean SBP of 5 mmHg between the intervention and the control groups. Using a two-sample *t* test, alpha 0.05, beta 0.2, and assuming a common standard deviation of 10 mmHg, 128 patients are required. Assuming 20% drop out, 160 patients will be enrolled (80 per group). This sample size is also powered to detect a clinically meaningful difference of 5 points in the KDQOL-36 (alpha 0.05, beta 0.2, and assuming a common standard deviation of 10 points) [53].

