### Randomization and blinding

Participants will be randomized (1:1) to enhanced usual care (measurement of physical activity levels) or the exercise intervention. A randomized permuted block design (of 4 and 6) will be used. To optimize comparability of the two groups at baseline, randomization will be stratified by baseline eGFR (15–29 ml/min/1.73m^2^ and 30–44 ml/min/1.73m^2^). The randomization sequence will be computer generated using Stata/MP 15.1 (https://www.stata.com/) and allocation will be concealed by web-based central randomization using the Research Electronic Data Capture System (REDCap 8.8.2© 2018 Vanderbilt University). Due to the nature of the intervention, participants cannot be blinded to group assignment; however, the primary outcome is objectively measured (24-h ABPM).

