### Statistical analysis

All analyses will follow the intent-to-treat principle. The difference in mean 24-h ambulatory SBP between groups at 8 weeks (primary outcome) will be analyzed using a mixed linear-regression model including fixed-effects terms for time point (8 weeks, 24 weeks), intervention, their interaction, baseline eGFR, baseline 24-h systolic ABPM, and a random-effects term for participant. In the primary analysis, missing values will be multiply imputed (100 iterations), using a hot-deck approach drawing all 8-week values from the control group with replacement, within strata of age and gender [54, 55]. Estimates from the 100 datasets will be combined using Rubin’s method [56]. Complete-case results, per-protocol and last-value-carried-forward results will be presented as sensitivity analyses. Estimates and corresponding 95% confidence intervals (CIs) will be reported for the overall difference at week 8 (and 24 weeks), adjusting for baseline eGFR and BP. All continuous outcomes with repeated measurements will be examined using mixed linear regression, following an outline similar to above. Continuous measurements without repeated measurements will be examined using linear regression, adjusting for baseline value. Residual, leverage and influence diagnostics will be examined. *P* values < 0.05 will be considered statistically significant. Adverse events will be tabulated, and compared between groups using Fisher’s exact test. All analyses will be completed in Stata/MP 15.1 (www.stata.com/).

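### The 80% power is calculated as if dropouts leave the analysis, but the primary analysis fills missing exercise-arm values from controls; at 20% missing 8-week data, power on the plan's own t-test basis is about 65-68%

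*Protocol article*

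**What the plan says.** The Sample size section of the protocol article says that "this study is powered to detect a clinically important difference in mean SBP of 5 mmHg between the intervention and the control groups". It uses a two-sample t test with "alpha 0.05, beta 0.2, and assuming a common standard deviation of 10 mmHg, 128 patients are required", and then allows for attrition: "Assuming 20% drop out, 160 patients will be enrolled (80 per group"). Allocation is equal (Randomization and blinding).

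The Statistical analysis section commits all analyses to intention to treat. It specifies a mixed linear model for the 8- and 24-week values, adjusted for baseline eGFR and baseline 24-h systolic pressure. In the primary analysis missing values are multiply imputed 100 times, "using a hot-deck approach drawing all 8-week values from the control group with replacement, within strata of age and gender", and the results are combined by Rubin's method. Analyses without this imputation are secondary: "Complete-case results, per-protocol and last-value-carried-forward results will be presented as sensitivity analyses".

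The Feasibility criteria section sets two separate targets: drop-out below 20% and missing outcome data below 10%.

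**The concern.** The two sections describe different analyses. Dividing 128 by 0.8 makes sense if the 20% are lost and the remaining 64 per arm show the whole 5 mmHg. That matches a complete-case test, which the article lists only as a sensitivity analysis. Under the primary analysis nobody is lost. Each exercise participant with no 8-week reading receives a control participant's value, so the expected contribution to the treatment difference is zero. The contrast being tested therefore shrinks with exercise-arm missingness, and the Sample size section makes no allowance for this.

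At stake is whether the trial has the power it claims, under its own drop-out assumption, for the difference it calls clinically important.

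**Working it through.** **Inputs.** From Sample size: difference 5 mmHg, SD 10, alpha 0.05, power 0.80, drop-out 20%, 80 per arm. From Statistical analysis: control-donor hot deck and Rubin's rules. Sidedness is not stated; two-sided is assumed because it reproduces 128.

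**1. The plan's own figures.** With an exact two-sided t test, 63 per arm gives 79.5% power and 64 per arm gives 80.1%, so the total is 128. Then 128/0.8 = 160. Both figures reproduce.

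**2. Expected estimate at 20% missing per arm.** Averaged over imputations, the exercise mean is 0.8 × (observed exercise mean) + 0.2 × (observed control mean), and the control mean is the observed control mean. The estimate is therefore 0.8 × (observed difference), and 0.8 × 5 = 4.0 mmHg.

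**3. True sampling variance.** 0.64 × (100/64 + 100/64) = 2.0, so the SD is 1.41.

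**4. Variance that Rubin's rules report.**
- Within imputation: 100/80 + 100/80 = 2.5.
- Between imputations: 2 × (16/80)² × 100/16 = 0.5.
- Total: 3.0, so the SE is 1.73.

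The reported SE exceeds the true spread because the imputed values reuse the observed controls.

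**5. Power.** P(Z > (1.96 × 1.73 − 4)/1.41) = P(Z > −0.43), about 67%. Under no effect, 2 × P(Z > 1.96 × 1.73/1.41) is about 1.6%.

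**6. Simulation of the planned imputation** (80 per arm, 8-week values only). The mean estimate is 4.0-4.1 mmHg and power is 65-68%. Rubin's SE is about 1.74 against a true SD of up to 1.43. Type I error is about 1.5-1.7%. The complete-case test on the same data has 80% power.

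**7. Dependence on what the article does not fix.** The baseline correlations are assumed, since none is given.

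| Setting | Power |
|---|---|
| 20% missing, unadjusted | 65-68% |
| 15% missing, unadjusted (estimate 4.25) | about 73% |
| 10% missing, unadjusted (estimate 4.5) | about 79% |
| 20% missing, baseline-adjusted, SD 10 unadjusted; correlation 0.3 / 0.5 / 0.7 | 67-69% / 72-75% / 80-84% |
| 20% missing, baseline-adjusted, SD 10 already residual; correlation 0.3 / 0.5 / 0.7 | 63% / 59% / 47% |

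The last row falls as correlation rises because the hot deck ignores each participant's baseline, so the imputed values carry the full unadjusted spread.

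**The case against.** **The real analysis is not a t test.** It adjusts for baseline pressure, and at a correlation near 0.7 with an unadjusted SD of 10 the power returns to 80% or more. This stands as a limit on the size of the shortfall. It does not rescue the statement, because the article gives neither the correlation nor the meaning of SD 10, and reading 10 as a residual SD makes the loss larger.

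**Fewer than 20% may be missing at week 8.** The endpoint is at 8 weeks in a 24-week trial, and the target for missing outcome data is under 10%. At 10% missing, power is about 79% unadjusted. With adjustment and an unadjusted SD of 10 it is about 82% at correlation 0.3, and higher at 0.5 and 0.7. This also stands. Even so, the Sample size section inflates by 20%, and its claim should hold under its own assumption.

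**The 5 mmHg may be the intention-to-treat difference.** The wording permits this. Those observed would then differ by 5/0.8 = 6.25 mmHg. Steps 3 to 5 give P(Z > (1.96 × 1.73 − 5)/1.41), about 87%, and the shortfall disappears. But the article does not say so, and removing dropouts in the inflation fits poorly with that reading.

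**Control-based imputation is a deliberate conservative choice.** Agreed. A reader might infer that the primary analysis is wrong and must be replaced, or that last value carried forward must be dropped. The document does not support either step. The imputation is prespecified, it errs against the intervention, and an unimputed result is promised. If dropouts really lose the benefit, 4 mmHg is the as-randomised effect and the observed-data model would overstate it.

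**KDQOL-36.** A reader might infer that the second power claim, "This sample size is also powered to detect a clinically meaningful difference of 5 points in the KDQOL-36", fails in the same way. That is not established: the imputation is tied to the primary analysis, and other repeated outcomes are promised only a similar outline.

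**Conclusion.** The mismatch between the power calculation and the primary analysis is real; 128 and 160 are not wrong as arithmetic. The primary analysis targets about 4 mmHg with about 65-68% power, instead of 5 mmHg with 80%, under these conditions:
- 20% of 8-week values are missing in each arm (only exercise-arm missingness dilutes the effect);
- the difference among those observed is 5 mmHg with SD 10;
- the t-test basis is used, with no gain from baseline adjustment.

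About one real effect in three would then be missed, where the plan intends one in five. Part of the loss comes from the conservative Rubin variance.

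It would be too strong to say that the trial simply has 67% power: plausible alternative inputs give anything from 47% to above 80%. What the document supports is that its power statement does not describe its primary analysis, and that the shortfall cannot be pinned down from what is stated. There is no inflated false-positive risk. Should be fixed.

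**What to change.** - In Sample size, say whether 5 mmHg is the difference among completers or the diluted intention-to-treat difference, and whether SD 10 is unadjusted or residual.
- Restate power for the analysis that will be primary, over 10-20% missing 8-week values and a range of baseline correlations. The control-based imputation can remain primary if that is wanted.
- In Statistical analysis, name as a sensitivity analysis the same mixed model fitted without imputation to all observed 8- and 24-week values. Complete case may already mean this, but it can also mean only participants with every visit.
- State whether the imputation applies to KDQOL-36, and restate that power only if it does.

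The cost is wording, with no extra patients or data. The downside is that the quoted power becomes less favourable under the completer reading.

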### Statistical analysis

All analyses will follow the intent-to-treat principle. The difference in mean 24-h ambulatory SBP between groups at 8 weeks (primary outcome) will be analyzed using a mixed linear-regression model including fixed-effects terms for time point (8 weeks, 24 weeks), intervention, their interaction, baseline eGFR, baseline 24-h systolic ABPM, and a random-effects term for participant. In the primary analysis, missing values will be multiply imputed (100 iterations), using a hot-deck approach drawing all 8-week values from the control group with replacement, within strata of age and gender [54, 55]. Estimates from the 100 datasets will be combined using Rubin’s method [56]. Complete-case results, per-protocol and last-value-carried-forward results will be presented as sensitivity analyses. Estimates and corresponding 95% confidence intervals (CIs) will be reported for the overall difference at week 8 (and 24 weeks), adjusting for baseline eGFR and BP. All continuous outcomes with repeated measurements will be examined using mixed linear regression, following an outline similar to above. Continuous measurements without repeated measurements will be examined using linear regression, adjusting for baseline value. Residual, leverage and influence diagnostics will be examined. *P* values < 0.05 will be considered statistically significant. Adverse events will be tabulated, and compared between groups using Fisher’s exact test. All analyses will be completed in Stata/MP 15.1 (www.stata.com/).

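### The primary test (control-donor hot deck pooled by Rubin's method) is conservative, so the stated alpha of 0.05 and 80% power after 20% dropout are not its actual properties

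*Protocol article*

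**What the plan says.** The Protocol article, Statistical analysis, makes multiple imputation the primary analysis. It creates 100 datasets "using a hot-deck approach drawing all 8-week values from the control group with replacement, within strata of age and gender". The donors are controls whichever arm the missing value belongs to. For pooling, "Estimates from the 100 datasets will be combined using Rubin’s method [56"; no other variance estimator is named. The decision rule is that P "values < 0.05 will be considered statistically significant". Complete-case, per-protocol and last-value-carried-forward results are sensitivity analyses, and other repeated continuous outcomes follow a similar outline.

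The Sample size section says that "this study is powered to detect a clinically important difference in mean SBP of 5 mmHg". It uses a two-sample t test with "alpha 0.05, beta 0.2, and assuming a common standard deviation of 10 mmHg, 128 patients are required", raised to 160 (80 per group) for 20% dropout. The Feasibility criteria separately set a target of less than 10% missing outcome data.

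**The concern.** Drawing an exercise participant's missing value from controls pulls the estimated difference towards zero and also makes that estimate vary less from trial to trial. Rubin's formula does not register the second effect. Its within-imputation part treats all 160 completed values as independent, and its between-imputation part adds to that. The positive covariance between arms created by the shared donors is ignored. A smaller estimate is therefore divided by a standard error that has not become smaller.

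At stake is whether the two figures on which the trial was sized, alpha 0.05 and 80% power with 20% dropout, describe the test that will decide the primary question. If they do not, a real 5 mmHg effect could be missed more often than the protocol implies, and readers would have no warning of it.

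**Working it through.** **Inputs.** From Sample size: difference 5 mmHg, SD 10 mmHg, alpha 0.05, beta 0.2, 128 evaluable, 20% dropout, 160 enrolled. From Statistical analysis: 100 imputations, control donors, Rubin pooling. From Feasibility criteria: missing outcome data below 10%. Assumed, because the article does not give them: a two-sided test, missingness equal in both arms and unrelated to outcome, the correlation between baseline and week-8 SBP, and the number of age-by-gender strata.

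**The plan's own figure.** An exact two-sided t test needs 64 per arm, or 128, with power 80.1%. 128/0.80 = 160. Both stated numbers reproduce and are not in dispute.

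**Closed form** (n = 80 per arm, fraction m missing in each, no covariates, many imputations).

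- The completed exercise mean is about (1 - m) × observed exercise mean + m × observed control mean. The completed control mean is about the observed control mean. The difference is therefore (1 - m) × the observed difference.
- Actual variance = (1 - m)² × 2 SD²/[n(1 - m)] = 2.5(1 - m).
- Rubin's variance = within + between = 2 SD²/n + 2m SD²/n = 2.5(1 + m).
- SE ratio = √[(1 + m)/(1 - m)]. Type I error = 2 P(Z > 1.96 × ratio).
- Power = P(Z > 1.96 × ratio - 5(1 - m)/actual SE).

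| Missing per arm | Actual variance (SE) | Rubin variance (SE) | SE ratio | Type I error | Power at 5 mmHg |
|---|---|---|---|---|---|
| 5% | 2.375 (1.54) | 2.625 (1.62) | 1.05 | 3.9% | 85% |
| 10% | 2.25 (1.50) | 2.75 (1.66) | 1.11 | 3.0% | 80% |
| 20% | 2.00 (1.41) | 3.00 (1.73) | 1.22 | 1.6% | 67% |

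For 20%: 1.96 × 1.2247 = 2.40 and 4.0/1.414 = 2.83, so power = P(Z > -0.43) = 67%.

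**Simulation** (80 per arm, 100 imputations, four strata, baseline-adjusted week-8 model, Rubin degrees of freedom, 4,000 trials per setting).

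- At 20% missing, type I error was 1.8%, 1.7% and 1.0% for baseline correlation 0, 0.5 and 0.7. The SE ratio was 1.19–1.32.
- Rejection at 5 mmHg was 65% at correlation 0 and 73% at 0.5, against 79% and 89% for complete cases. It reaches about 80% only near correlation 0.7.
- A two-time-point random-intercept model, 1 to 6 strata and a Bayesian-bootstrap hot deck gave similar results. All settings with 20% missing in both arms fell at about 1.0–2.3%.
- At 10% missing, most runs fell at about 2–3%, with extremes of 1.8% and 3.7%.
- With nothing missing, type I error was 4.7% and the SE ratio 1.00, so the shortfall comes from the imputation and pooling.

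**Unequal missingness** (closed form). 30% exercise/10% control gives 0.65% (ratio 1.39). 10% exercise/30% control gives 3.4% (ratio 1.08). The direction does not change.

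**The case against.** The strongest reply is that a test with size below 5% still controls false positives at 0.05, and that the larger variance is a defensible choice under control-based imputation. Much of this stands.

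- **Precision.** A reader might infer that Rubin's method throws away precision that the trial has paid for. The plan's figures do not support that. The design precision for 128 completers is 10 × √(2/64) = 1.77 mmHg, and Rubin's SE of 1.73 is about the same. The repeated-sampling SE of 1.41 is smaller than the SE with all 160 observed, 10 × √(2/80) = 1.58, which is an awkward benchmark for how wide an interval ought to be.
- **Replacement.** A reader might also infer that Rubin's variance is simply wrong and must be replaced. Which variance to use here is disputed among statisticians. With a matching SE the factor (1 - m) cancels: 4.0/1.41 and 5/1.77 both equal 2.83. The test becomes essentially the complete-case test, which the article already lists as a sensitivity analysis, and missing exercise outcomes would no longer be penalised.
- **The 20% figure.** It is planned dropout, not a stated week-8 missing rate. At the upper bound of the 10% feasibility target the effect is smaller, and closed-form power without covariates is still about 80%.
- **Dilution.** Part of the shortfall can equally be described as the effect shrinking from 5 to about 4 mmHg. Against Rubin's SE the expected statistic is 4.0/1.73 = 2.31, where the design assumed 2.83.

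What the reply does not remove is the mismatch in the article. It sizes the trial for 80% power after 20% dropout, names a different analysis as primary, and does not say that this analysis is deliberately conservative.

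**Conclusion.** The point holds in limited form. As written, the primary test is conservative: about 1–2% two-sided type I error at 20% missing per arm and about 2–3% at 10%. Its intervals are about 20–30% and 10–20% wider, respectively, than the repeated-sampling variability of the estimate. At the dropout that the protocol plans for, power for 5 mmHg is about 65–67% without baseline correlation and about 73% at 0.5, not 80%.

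These figures rest on equal, outcome-unrelated missingness, SD 10 and 80 per arm. The baseline correlation is unknown, so no single alpha such as 1.6% should be read as a fixed property of the trial. Nothing here suggests excess false positives, an error in the 128/160 arithmetic, or that Rubin's method has to be abandoned.

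**What to change.** 1. In Statistical analysis, state that the primary control-donor analysis with Rubin's variance is conservative, and give its approximate type I error at 10% and 20% missing.
2. In Sample size, state that 128/160 describes a complete-case t test, and give the power of the primary analysis at 10% and 20% missing under a stated range of baseline correlations.
3. Add a sensitivity result: resample participants within arm and eGFR stratum, repeat the hot deck and the model in each resample, and take the SE, 95% CI and P value from that distribution. Do the same for other repeated outcomes that use this outline.

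The first two changes cost a few sentences. The third costs programming and substantial computing time, since imputation and model are refitted in every resample, but no new data or patients. A simplified bootstrap (stratum donor means in place of 100 draws, 200 resamples, week-8 model, correlation 0.5, 1,000 trials) gave 4.4% type I error and 88% rejection at 5 mmHg. The full procedure should be checked before it is relied on.

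Making the bootstrap the primary variance is the sponsor's decision. It would bring the test near its nominal level, at the price of a narrower interval and a P value close to the complete-case one, so that missing data would no longer count against the intervention.
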